#### Aim 2, I-TRANSFER implementation

We expect approximately 60 stakeholders to comprise the Aim 2 sample. Acute care and HHC site champions including hospitalists, emergency room physicians, programmers, managers, sepsis experts, ambulatory providers, care coordinators, Directors of Nursing, home health liaisons, intake personnel and nurses, are the expected subjects. After informed consent, they will be administered the ORIC survey and interviewed by the study team using the CFIR interview guide.

### Measures and outcomes

#### Aim 1, effectiveness of the I-TRANSFER intervention

The primary outcome of Aim 1 is 30-day all-cause hospital readmissions. Secondary outcomes are number of inpatient days (if rehospitalized), and ED use within 30 days, all measured through the Medicare Administrative Data.

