## Methods

### Study aims and hypothesis

#### Aim 1, effectiveness of the I-TRANSFER intervention

Aim 1 of our study is to test the effectiveness of the I-TRANSFER intervention compared to usual care on 30-day rehospitalization and emergency department (ED) use among sepsis survivors receiving HHC. We hypothesize that compared to usual care, sepsis survivors who receive the I-TRANSFER intervention will have significantly fewer all-cause 30-day rehospitalizations, inpatient days if rehospitalized, and ED visits within 30 days of hospital discharge.

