### Study period

Onboarding is a 6-month period when the implementation and research teams plan the implementation. Intervention is the 12-month period when I-TRANSFER is in operation. Maintenance is a 6-month period when the research team assesses whether the intervention continues without research team monitoring and feedback. The analysis will be an intent to treat. We will adjust for time, or any health system interventions, as well as patient covariates that may confound the findings using generalized mixed models.

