### Study sample

#### Aim 1, effectiveness of the I-TRANSFER intervention

Sample sizes needed to provide sufficient power were calculated using Stata [79]. Preliminary unpublished data of a national sample show on average a 23% 30-day readmission rate for sepsis survivors in HHC. Our previous study showed a 7-percentage point or 41% relative reduction among those receiving early visits [24], and other studies report that 22–45% of readmissions are preventable [80]. Therefore, to detect a 7-point reduction (30.4% relative decrease) in the readmission rate under the intervention we would require an average of 400 patients per time interval. Current estimates from the sites give us 869 per period.

The I-TRANSFER intervention is targeted at the hospital and HHC agency and is considered part of clinical care implemented for all sepsis survivors. There is no individual patient recruitment, prospective assignment, or primary data collection from patients. The analysis will be completed on existing datasets. We will analyze a sample drawn from all Medicare fee-for-service sepsis survivors discharged to HHC during a 4-year period (01/01/2021 and 12/31/2024). Analyses from our 2013–14 dataset suggests that without exclusions there will be approximately 800,000 sepsis discharges per year who receive HHC [24].

Ten clinical sites located in the United States have committed to participate as dyads, 5 referring hospitals and their 5 partnered home health agencies. Sites were selected based on our relationships with staff, ownership status (hospital owned or free-standing), commitment to appoint an implementation team, size, geography, and diversity (academic and community). We sought regional diversity with sites in the East and West. To be eligible HHC agencies must be Medicare certified to generate claims and confirm a hospital referral source as a partner.

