### Analysis

#### Aim 1, effectiveness of the I-TRANSFER intervention

A key initial task is the identification of all sepsis survivors in the national hospital dataset. Consistent with our prior work, we will use two complementary strategies to identify sepsis survivors. First, we will use the explicit International Classification of Diseases 10th Revision (ICD-10) codes (A40-41, R65.2). Second, we will employ the implicit approach used in our previous study and developed by Angus and colleagues [88] that requires a code for infection and end-organ dysfunction. Among them we will identify the sepsis survivors transitioned from participating hospitals to their partner HHC agency during the study timeframe by merging the Provider of Service File with the claim files.

Each hospital discharge of a sepsis survivor to HHC will represent a separate record on the timeline file. Some Medicare beneficiaries will have more than one index hospital discharge during the study period. Data available will give us the flexibility to define an “index” hospitalization in several ways. Our main approach will be to analyze all eligible hospitalizations followed by HHC and to adjust for the potential effect of clustering at the patient and provider level. We plan to examine the sensitivity of our results to alternative specifications of the “index” hospital stay including analyses based on a single index hospitalization per person.

Deidentified Medicare claims will be the source of information used to construct Aim 1 outcomes of rehospitalization, total hospital days if readmitted and ED utilization. The CMS claims will be stored a secure, password protected site. The CMS approach to identifying hospital readmissions was successfully used in our heart failure and sepsis studies and we will use the same approach to identify readmissions in this study [24, 50]. Observations on sepsis survivors in the baseline period will be used to check balance on covariates identified by the Andersen Behavioral Model. Any remaining imbalance will be considered by including covariates in the hierarchical regression analysis.

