In addition to the survivors from the treated dyads in the baseline period, additional control survivors will be used to provide a much larger sample of control observations. These observations will be drawn from the population of Medicare sepsis survivors not being cared for by any of the participating institutions. This sample is unlikely to be balanced on covariates, a priori, with the sample of survivors from participating providers. Therefore, entropy balancing will be used to create sampling weights for these observations to produce balance on covariates. All hierarchical regression analyses will take these entropy balance weights into account. In addition to an intent-to-treat indicator, the regression will include covariates specified by the Andersen Behavioral Model. Inpatient days after the index discharge will be modeled using hierarchical Poisson regression. ED utilization will be modeled using hierarchical logistic regression.

The pragmatic aspects of the study design make it important to conduct various sensitivity and exploratory analyses. Sensitivity analyses will include checks of robustness of findings with and without sepsis survivors who are readmitted shortly after discharge (e.g., within 7 days), those with a resumption of HHC episode, discharges with very short (1 day) or very long hospital stays (30 days or more), and survivors less than 65 years old. Exploratory analyses will include estimation stratified by type of sepsis, sex (as a biological variable), and hospital ownership status.

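### Inpatient days are defined only for rehospitalized patients, a group the intervention is meant to change, so the contrast is not interpretable and does not match the model sentence

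*Protocol article*

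**What the plan says.** Three places in the protocol article tie inpatient days to readmission:

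- Study aims and hypothesis, Aim 1: fewer "inpatient days if rehospitalized, and ED visits within 30 days of hospital discharge" are expected under I-TRANSFER.
- Measures and outcomes, Aim 1: "Secondary outcomes are number of inpatient days (if rehospitalized), and ED use within 30 days". The same section makes 30-day all-cause readmission the primary outcome.
- Analysis, Aim 1: the outcomes built from claims are "rehospitalization, total hospital days if readmitted and ED utilization".

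The sentence that names the model, later in Analysis, Aim 1, does not repeat the condition: "Inpatient days after the index discharge will be modeled using hierarchical Poisson regression". It also does not say that discharges without readmission enter with zero days.

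Under Study period the article states: "The analysis will be an intent to treat". Under Study sample, Aim 1, the planning assumption is "on average a 23% 30-day readmission rate for sepsis survivors in HHC", with a 7-point reduction to be detected.

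**The concern.** The condition for entering the inpatient-days comparison occurs after the intervention starts, and it is the event the intervention is designed to prevent. If I-TRANSFER works, some patients who would have been readmitted under usual care are missing from the intervention side. The patients left are not the counterpart of the readmitted controls.

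The planned adjustment does not repair this. The entropy weights balance outside controls against the survivors from participating providers as a whole, not within the readmitted subset. Covariates cannot be relied on to capture whatever separates a prevented readmission from one that was not prevented. Study sample, Aim 1, itself cites studies in which 22–45% of readmissions are preventable, so the plan already treats some readmissions as different in kind.

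At stake is a stated hypothesis. Fewer days among the rehospitalized could be refuted, or shown as no effect, in a trial where the intervention reduced hospital use. It could also appear confirmed for reasons unrelated to how long any given patient stays.

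**Working it through.** **Inputs.** From the article: 23% control readmission and a 7-point reduction, so 16% under intervention; 869 patients per period. Assumed, because the article gives no length of stay for readmissions: remaining readmissions average 7 days in both groups, and prevented readmissions average *s* days.

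**The plan's own figure.** 7/23 = 30.4%, which matches the stated relative decrease. The article gives no planning figure for inpatient days.

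**Size of the conditional groups.** 869 × 0.23 ≈ 200 readmitted controls; 869 × 0.16 ≈ 139 readmitted intervention patients. The comparison sets 200 against a selected 139.

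**Formulas, per 100 discharges.**

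- Control mean days if readmitted = (7*s* + 16 × 7)/23. Intervention mean = 7.0.
- Control total days = 7*s* + 112. Intervention total = 112.

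| Prevented stay *s* | Control mean if readmitted | Intervention mean | Conditional change | Days per 100 discharges | Change |
|---|---|---|---|---|---|
| 3 | 133/23 = 5.78 | 7.0 | +21% | 133 to 112 | -16% |
| 4 | 140/23 = 6.09 | 7.0 | +15% | 140 to 112 | -20% |
| 6 | 154/23 = 6.70 | 7.0 | +5% | 154 to 112 | -27% |
| 7 | 161/23 = 7.00 | 7.0 | 0% | 161 to 112 | -30% |
| 8 | 168/23 = 7.30 | 7.0 | -4% | 168 to 112 | -33% |

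The conditional change runs from positive through zero to negative, while hospital use falls in every row.

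**Second parameterisation.** Fix the control mean at *m* days, so the intervention mean is (0.23*m* - 0.07*s*)/0.16. With *m* = 6 and *s* = 3 this is (1.38 - 0.21)/0.16 = 7.31, a ratio of 1.22. Days per discharge fall from 1.38 to 1.17, a ratio of 0.85. Over *m* = 5 to 8 and *s* = 2 to 4, the conditional ratio is 1.09 to 1.33 and the all-discharge ratio 0.76 to 0.92. With *s* = *m* the ratios are 1.00 and 0.70: a 30% fall in bed-days appears as no effect.

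**Poisson, separately.** With an assumed mean of 6 to 6.5 days and SD of 4 to 6 days among the readmitted, variance/mean runs from 16/6 = 2.7 to 36/6.5 = 5.5. For a plain Poisson test, two-sided type I error is 2 × P(Z > 1.96/√dispersion), about 23% to 40%. This is an upper illustration for a model without random effects or robust variance, which is not the planned model.

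**The case against.** Four points can be made for the plan.

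1. **The model sentence omits the condition.** It follows a description of regressions with an intent-to-treat indicator, so an all-discharge count is not excluded. This stands in part. A reader might infer that the plan firmly restricts the analysis to readmitted patients, but the article does not settle that. Nor does the sentence cure the problem: nowhere is a patient without readmission said to count as zero, and three statements say otherwise. Either reading calls for a correction.

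2. **The direction depends on assumed stays.** This stands. A reader might infer that an effective intervention will appear to lengthen stays. That needs prevented stays to be shorter than average, which is plausible but unsupported by any figure in the article. At 8 days the sign turns, and a true shortening of the remaining stays would also offset the selection.

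3. **The Poisson model is hierarchical.** The main approach also adjusts for clustering by patient and provider. Only some beneficiaries have more than one index discharge, so a patient-level effect would lie close to a discharge-level one and could absorb much of the excess variance. This stands. A reader might infer that the p-values will be too small and take 23% to 40% as the trial's error rate, but the documents do not support that. The selection problem arises under any model restricted to the readmitted.

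4. **Readmission is reported beside it.** Readmission and days given readmission are the two parts of a two-part model. True, but the second part alone is not an intervention effect. Only the combination recovers it: with *s* = 4, 0.23 × 6.09 = 1.40 against 0.16 × 7.0 = 1.12 days per discharge.

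**Conclusion.** The point holds for the conditioning and for the mismatch between sections. Defining inpatient days only among the rehospitalized compares groups selected by the primary outcome, which conflicts with the stated intent-to-treat analysis. The sign of the contrast is not interpretable: on the plan's 23% to 16% and an assumed 7-day remaining stay, it moves from +21% to about -4% as the prevented stay goes from 3 to 8 days, while days per discharge fall by 16% to 33%.

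The loss of comparability follows from the plan's own hypothesis. The sizes rest on assumed stay lengths and on remaining stays being unaffected. The outcome is secondary, and the primary analysis of readmission is untouched. Overdispersion is a reason to specify the count model with care. It is not evidence that the planned hierarchical model gives wrong error rates.

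**What to change.** - Define the outcome as inpatient days within 30 days of index discharge for every index discharge, with zero if not readmitted. Report deaths without readmission alongside, because a patient who dies at home would otherwise score as a good result.
- Reword the hypothesis under Study aims and the definitions under Measures and outcomes and Analysis so that they agree with each other and with the model sentence.
- Report days among the readmitted as description only, without a test of the intervention.
- Many zeros and variable stays make overdispersion likely. Use a negative binomial or two-part hierarchical model, or a hierarchical Poisson model that explicitly allows overdispersion, for example through a discharge-level random effect. If a two-part model is used, report the combined effect on mean days per discharge.
- Do not rely on dyad-robust variance: with five participating dyads it can itself give intervals that are too narrow.

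The cost is a change of wording and model specification. The Medicare claims, the sample and the primary analysis are unchanged.

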#### Aim 2, I-TRANSFER implementation

The outcomes of Aim 2 will be the alternative approaches in workflow, barriers, facilitators, and differences in acceptability observed between the study sites during implementation of the I-TRANSFER protocol. These alternative approaches will be noted, compared, contrasted, and reported as study results so agencies with similar barriers can see suggested solutions to increase generalizability of the findings.

### Data sources and collection

#### Aim 1, effectiveness of the I-TRANSFER intervention

A national sample of Medicare administrative, home health OASIS and claims data from CMS Chronic Condition Warehouse (CCW) will be employed (Table 1). This will yield detailed information about the index hospital stay, subsequent HHC and outpatient provider services and outcomes. It also will provide information about the characteristics of hospitals and admitting HHC agencies, and the health care market areas where patients live. The CCW maintains calendar year files so we will request files between 01/01/2021 and 12/31/2024. We will request CCW data on all Medicare beneficiaries with a claim for a HHC service provided one year prior to the start of the study to 6 months after the end. Within these data sets, we will identify the sepsis survivors transitioned from participating hospitals to their partner HHC agency by merging the Provider of Service File with the claim files. The additional sepsis survivors found in the CCW data, not associated with our participating institutions, will serve as additional controls.

**Table 1 Tab1:** Variables Obtained from the Medicare Claims and OASIS Home Health Admission Files

Data	Source
*Physician, Home Health Agency and Hospital Characteristics*	
Physician specialty	Downloadable National Provider Identifier File (CMS)
Home Health Agency and Hospital Ownership	Provider of Services File
Home Health Agency and Hospital Control/auspices (for- profit/non-profit/public)	Provider of Services File
Size of home health agency, # of annual admissions	Provider of Services File
*Beneficiary Sociodemographic, Clinical and Cost Variables*	
Demographics	Medicare Beneficiary Summary File; OASIS
Informal support	OASIS
Living arrangements	OASIS
Eligible for Medicare and Medicaid	Medicare Beneficiary Summary File
Health care use and cost (ie. Medicare program payments)	MedPAR/Medicare Parts A and B SAF claims
Medical diagnoses ICD codes, acute and HHC	MedPAR/Medicare Parts A and B SAF claims; OASIS
Index hospital length of stay	MedPAR
Cognitive, physical, sensory function	OASIS
*Early Nursing and Outpatient Provider Visits Following Index Hospital Discharge*	
Timing and number of home health visits	Medicare Home Health SAF claims
Timing of first physician, physician assistant or nurse practitioner visit for outpatient evaluation & mgt	Mediare Part B SAF claims
*Beneficiary Readmission Outcomes, Mortality and Other Outcomes after Home Health Admission*	
Timing and number of Medicare inpatient hospitalizations and ED use	MedPAR
Inpatient admission reason	MedPAR
Cognitive, physical, sensory function	OASIS
*Early Nursing and Outpatient Provider Visits Following Index Hospital Discharge*	
Timing and number of home health visits	Medicare Home Health SAF claims
Timing of first physician, physician assistant or nurse practitioner visit for outpatient evaluation & mgt	Mediare Part B SAF claims
*Beneficiary Readmission Outcomes, Mortality and Other Outcomes after Home Health Admission*	
Timing and number of Medicare inpatient hospitalizations and ED use	MedPAR
Inpatient admission reason	MedPAR

Source files will also include: (1) the CMS Provider of Services file containing information on hospital, home health, and other provider characteristics such as ownership and length of participation in the Medicare and Medicaid programs; (2) the Area Health Resources file which is a national, county-level record of the supply of health care services maintained by the US Health Resources and Services Administration; and (3) Census data that include ZIP-code level socio-economic measures for the patients’ place of residence.

The OASIS is a comprehensive assessment tool designed to collect nearly 100 items related to a home health recipient’s functional status, clinical status, and service needs at several time points during a HHC episode. Mandated by CMS since 1999, the OASIS is the most comprehensive national data set on HHC patients. OASIS data are collected upon admission, every 60 days, if transferred to an inpatient facility, and at discharge. The OASIS will be the source of detailed patient clinical data including, importantly, functional status, health therapies, the result of a drug regimen review and whether patient-specific parameters have been established for notifying the physician of changes in vital signs or other clinical findings. The reliability of OASIS functional items varies. Mobility and transferring have Kappa values > 0.70, while lower body dressing and bathing have Kappa values of 0.61 and 0.53, respectively. All other items to be analyzed in the proposed study have at least moderate reliability (Kappa ≥ 0.40) with the exception of eating and meal preparation (Kappa = 0.38 for both) which primarily will be used to control for differences in functioning on HHC admission [80].

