**Fig. 1 Fig1:**
[figure not shown]
Andersen Behavioral Model of Health Services. Health services system determinants

There are three types of Individual Determinants in the Andersen framework. Predisposing factors include age, sex as a biological variable, race, and informal support, for example. Enabling factors include facilitators of the use of health care services (e.g., health insurance, income). Need/illness level includes health status such as acute and chronic disease, cognitive and physical functioning, symptoms such as pain and anxiety, and recent prior hospitalizations. Determinants in the Andersen framework will also be considered for risk adjustment and when forming our national, covariate-balanced control sample (Aim 2). Conceptually, the outcomes are jointly determined by the determinants in the Andersen framework as well as the home health and physician services provided during the HHC episode. Because sicker patients are more likely to use more HHC and physician services and are likely to have worse outcomes – that is, the receipt of increasing levels of HHC and physician services is endogenous – a simple comparison of outcomes will yield misleading biased results and are taken into consideration in the analytic plan.

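### The index-discharge window and the claims files share the same start and end dates, and Table 1 sources ED use from MedPAR alone

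*Protocol article*

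**What the plan says.** All references are to the protocol article, Methods unless stated.

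- **Index discharges** (Study sample, Aim 1): "sepsis survivors discharged to HHC during a 4-year period (01/01/2021 and 12/31/2024".
- **Files requested** (Data sources and collection, Aim 1): "The CCW maintains calendar year files so we will request files between 01/01/2021 and 12/31/2024".
- **Span of the request** (same section, next sentence): beneficiaries "with a claim for a HHC service provided one year prior to the start of the study to 6 months after the end". The article gives no calendar date for the start or end of the study in this sense.
- **Outcomes** (Measures and outcomes, Aim 1): "The primary outcome of Aim 1 is 30-day all-cause hospital readmissions". The secondary outcomes are inpatient days if rehospitalized and "ED use within 30 days, all measured through the Medicare Administrative Data".
- **History covariate** (Conceptual framework, Aim 1): need or illness level includes "symptoms such as pain and anxiety, and recent prior hospitalizations". The same section says these determinants will be considered for risk adjustment and for forming the balanced national controls. No look-back length is given.
- **ED source** (Table 1): the row "Timing and number of Medicare inpatient hospitalizations and ED use" names MedPAR and nothing else. The row is printed twice, the same both times.

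**The concern.** A 30-day outcome needs 30 days of claims after the index discharge, and a history covariate needs claims before it. When files and index dates coincide, neither is available at the edges of the window. The article states no earlier stop for index discharges. A readmission that falls after the last file date would not be seen, and unless those discharges are excluded or censored, the latest rates would look too low.

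At the other edge, the earliest discharges precede the intervention, so they are controls. Under-recorded prior hospitalizations among them would make the covariate mean something different in early control records than in later intervention records. That covariate is a candidate for both the entropy weights and the regressions.

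ED use is a separate hypothesis (Study aims), a separate secondary outcome and a separate logistic model (Analysis, Aim 1). If its source records only inpatient stays, it captures only ED visits that became admissions and adds little to the primary outcome.

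**Working it through.** **1. The window.** 01/01/2021 to 12/31/2024 inclusive is 1461 days, or 4.0 years. This reproduces the four-year period stated under Study sample. The files requested cover exactly the same days.

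**2. End of window.** The last discharge with 30 days of claims is 12/31/2024 minus 30 days = 12/01/2024. Discharges from 12/02 to 12/31/2024 are short: 30 / 1461 = 2.1% of the window, assuming an even flow of discharges. Full follow-up through 12/31/2024 would need claims to 01/30/2025.

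**3. Readmissions unseen in those 30 days.** Inputs: a 23% readmission rate (Study sample, Aim 1) and 33% of 30-day readmissions within 7 days (Background). Assumption: readmissions are even within days 1–7 and within days 8–30. With k days of claims, the share seen is

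F(k) = 0.33k/7 for k ≤ 7, then 0.33 + 0.67(k − 7)/23.

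- Sum of F over k = 0 to 29: 1.32 + 7.26 + 7.37 = 15.95.
- Mean share unseen: (30 − 15.95)/30 = 0.468. Counting from mid-day (k = 0.5 to 29.5) gives 0.452.
- Rate understated in these discharges: 0.23 × 0.468 = 10.8 points.
- Share of all readmissions in the window: 14.05/1461 = about 1%.

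**4. Effect on a study period.** This depends on which period ends on the last file date, and the article does not say.

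| Period ending 12/31/2024 | Share truncated | Understatement of a 23% rate |
|---|---|---|
| 6-month maintenance | 30/184 = 16% | 0.23 × 14.05/184 = 1.8 points |
| 12-month intervention | 30/366 = 8% | 0.23 × 14.05/366 = 0.9 points |

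Study design and Study period place a 6-month maintenance period after the intervention. If the files cover it, the intervention ends at least six months before the files do, and the second line of the table does not arise.

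**5. Start of window.** The look-back length is not stated, so a range is shown.

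| Assumed look-back (days) | Share of the 1461-day window without full history |
|---|---|
| 30 | 2.1% |
| 90 | 6.2% |
| 182 | 12.5% |
| 365 | 25.0% |

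Study design describes a control year before contact with the team and then 6 months of onboarding. If both lie within the files, at least 18 months precede the intervention, so every discharge in this table is a control.

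**6. The two sentences on the request.** The second sentence adds 12 months before and 6 months after the study. The files cover 48 months.

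| Meaning of study | Months needed | Fits in 48? |
|---|---|---|
| The 2021–2024 window | 12 + 48 + 6 = 66 | No |
| Onboarding through maintenance | 12 + 24 + 6 = 42 | Yes, in length |
| Onboarding plus intervention | 12 + 18 + 6 = 36 | Yes, in length |

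**7. The ED row.** Table 1 side by side:

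- MedPAR alone: index hospital length of stay; inpatient admission reason; inpatient hospitalizations and ED use.
- MedPAR with Parts A and B SAF claims: health care use and cost; acute and home health diagnoses (the latter with OASIS).
- Part B SAF claims: timing of the first outpatient provider visit.

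The table names wider claims where they are meant. Apart from the ED half of one row, the MedPAR-only rows describe inpatient stays.

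**The case against.** The strongest reply is that the edges hardly touch the primary comparison. Maintenance follows the intervention, so intervention-period discharges should have full follow-up. The outcomes that Analysis, Aim 2 compares in maintenance are sepsis diagnoses and visit patterns, not readmission, and the visit pattern needs only about a week of claims. This stands, and it removes most of the force of the 0.9- and 1.8-point figures. Any remaining truncation would be shared in part by concurrent national controls.

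Second, the sentence after the file dates describes a one-year lead and a six-month tail, which fits in 48 months on two of three readings. That is fair, but it helps only once the study is dated. On any reading, the stated index window still ends on the day the files end.

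Third, a complete-follow-up rule could sit in the full protocol or analysis plan. It could, so it cannot be concluded that truncated discharges will be counted as not readmitted. Likewise, prior hospitalization is one example within a conceptual framework, and its weight in the analysis is not known.

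Fourth, on ED use, Analysis, Aim 1 names Medicare claims generally as the source of the Aim 1 outcomes, and Parts A and B SAF claims are already listed for health care use. This shows that the fault probably lies in one table row and not in the data requested. The article also never says what MedPAR contains, so the inpatient-stay reading is an inference from Table 1.

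**Conclusion.** The point holds in a limited form. The stated index window and file window coincide, which leaves 2.1% of the window without complete 30-day outcomes (even discharge flow assumed). Between 2.1% and 25% lacks full prior history for assumed look-backs of 30 to 365 days. The two sentences on the request conflict if study means the four-year window, and cannot be checked otherwise because the study is undated. Bias in the intervention-period readmission rate is probably small.

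The ED row matters more for what is measured. If MedPAR holds only stays, ED visits ending in discharge home are missed and the ED outcome largely overlaps readmission.

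A reader might infer that the request cannot deliver the study's measures, that the intervention's readmission rate will be biased by about a point, or that the ED hypothesis goes untested. The documents do not support these. The truncation is confined to the last 30 days, the intervention should end months earlier, and wider claims that may serve the ED outcome are already listed.

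**What to change.** 1. Set the last index discharge at 12/01/2024, or add early-2025 claims to at least 01/30/2025.
2. State one look-back length and apply it to every discharge. Either start index dates one look-back period after 01/01/2021, or obtain 2020 claims for look-back only. Study design sets 2020 aside as a comparison cohort, which does not bar that use.
3. Give calendar dates for the start and end of the study and reconcile the two sentences in Data sources and collection, Aim 1.
4. Change the Table 1 ED row to outpatient institutional plus inpatient claims, after confirming that both are within the Parts A and B SAF files already listed. Report ED visits without admission separately.

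**Cost.** At the end of the window, about one month of index discharges or one more file year, since files come by calendar year. At the start, either the 2020 file or the loss of control discharges for one look-back period (30 to 365 days over the range above). The ED change is a table correction with a little more analysis work.
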